##### Stage 3: selection of households

Within each selected cluster, a comprehensive list of households – defined according to the HDSS and spanning all settlements – will be extracted from the HDSS database. To ensure representativeness, this list will be randomized, and the first 40 households will be selected for inclusion. In clusters with fewer than 40 households across all the settlements, all households will be included. If the initially selected 40 households yield fewer than the expected number of eligible children, additional households from the randomly generated list will be sampled until the target is reached. Selected households will then be assigned to data collectors for field visits.

##### Stage 4: selection of children

From the selected households, a list of all eligible children will be made. To ensure adequate power and based on the simulations conducted, 70 children per cluster will be sampled from these households according to the following age group allocation: < 1 year (10 children); 1–4 years (40 children); 5–9 years (10 children); 10–14 years (10 children).

This allocation (ratio 1:4:1:1) was chosen because the study was powered based on the 1–4 years age group, which is key to assessing vaccine coverage and immunity profiles following MR1 and MR2. In households containing multiple children within the same age cohort, one child per cohort will be randomly selected, ensuring that no more than one child from each age group is chosen from the same household. Sampling in each cluster will continue until 70 children are recruited, yielding a total sample size of 1,750 children from 25 selected clusters. To avoid selection bias, the survey Statistician and Data Manager, instead of field teams, will be responsible for the selection of households and generating random list of children to be recruited from each cluster.

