### Study setting and population

The study will be conducted within the Basse and Farafenni Health and Demographic Surveillance Systems (BHDSS and FHDSS), located in the Upper River and North Bank Regions (URR and NBR) of The Gambia, respectively (Figure 2). The BHDSS and FHDSS collectively monitor approximately 250,000 individuals, representing about 10% of the country’s population [31]. With a combined annual birth cohort of about 8,000 infants, both HDSS sites conduct routine surveillance rounds every four months, collecting comprehensive health information, including vaccination and disease data from all consenting households within the communities.

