Consent from a guardian, rather than a parent, will only be accepted if both parents are deceased or if both parents are out of The Gambia for an extended period, leaving another adult to care for the child. Guardians cannot provide consent if the parent is in another part of The Gambia or temporarily out of the country. A certified copy of the completed ICD will be provided to the parent or caregiver after the consent is signed or thumb-printed. The outcome of the informed consent process (i.e. consented/did not consent) will be recorded in the study’s consent log. As part of the informed consent process, consent will also be sought for storage of samples, the future use of any remaining samples and associated data for ethically approved research intended to benefit the people of The Gambia.

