### Statistical analysis and modeling

#### Descriptive analysis

We will use the R package *survey* to account for the complex sampling design when estimating age-specific and location-specific measles and rubella seroprevalence. Sampling weights will be applied to ensure representativeness, given the probability proportional to size sampling across the 25 randomly selected clusters. The weights will be computed based on the inverse probability of selection and will be adjusted to account for differences between the projected and actual population sampled per age group in each cluster.

Seroprevalence estimates will be generated for the four age cohorts (under 1 year, 1–4 years, 5–9 years, and 10–14 years) and across the sampled districts. We will report overall, HDSS level, district, ward, and age-specific seropositivity estimates. All 95% confidence intervals will be computed using linearized Taylor series variance estimation. We will use T-tests to assess the significance of differences in weighted seroprevalence between subgroups (e.g. age, sex, district). Associations between seropositivity and predictor variables (age, sex, geographic location) will be analyzed using univariate and multivariate generalized linear regression models, adjusting for the survey weights. Both unadjusted and adjusted odds ratios (ORs) with 95% confidence intervals will be reported.

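### The stated weights cannot correct participation that differs by vaccination status; if under-vaccinated children take part less, seroprevalence is biased upward

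*Protocol article*

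**What the plan says.** All references are to the protocol article.

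- **Recruitment.** Stage 4 sets the stopping rule: "Sampling in each cluster will continue until 70 children are recruited". The stated total is 1,750 children in 25 clusters. It takes one child per age group per household, "ensuring that no more than one child from each age group is chosen from the same household". Stage 3 starts from 40 randomly ordered households. If these give too few eligible children, "additional households from the randomly generated list will be sampled until the target is reached".
- **Weights.** Stage 2 defines the cluster probability as a × d / b and the individual probability as c / a, where c is a number fixed in advance. The weight is the inverse of their product. Descriptive analysis keeps this basis and names one adjustment: the weights "will be adjusted to account for differences between the projected and actual population sampled per age group in each cluster".
- **Who can consent.** Under Informed consent procedure, a child whose parents are both under 18 cannot be enrolled, and "Guardians cannot provide consent if the parent is in another part of The Gambia". The result of each consent discussion goes into a log.
- **What is already held.** Study setting and population says that the HDSS sites run rounds every four months, "collecting comprehensive health information, including vaccination and disease data from all consenting households". Specimen and data collection uses these records only to supplement vaccination history.

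**The concern.** A stopping rule counted in recruited children fills every cluster to 70 whatever the response. The sample then looks complete, while its mix of vaccinated and unvaccinated children may differ from that of the children drawn. A weight that is constant within an age-by-cluster cell cannot restore the mix.

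Missed vaccination and non-participation may share causes, such as an absent parent, a young parent or reluctance towards health services. If so, seropositivity is overstated. The error would carry into the age- and location-specific immunity profiles, into the susceptible fraction used for outbreak risk, and into the comparison of indirect estimates with serology, where serology is the reference. Confidence intervals from the design would not show it.

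**Working it through.** **1. The plan's own figure.** 10 + 40 + 10 + 10 = 70 per cluster, and 25 × 70 = 1,750. This matches. The power simulation cannot be reproduced from the article's text, and this point does not depend on it.

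**2. The weight.** 1 / [(a × d / b) × (c / a)] = b / (d × c). The cluster size a cancels and no response rate enters. The age-by-cluster adjustment multiplies every child in a cell by the same factor, so the vaccinated-to-unvaccinated ratio within the cell is unchanged.

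**3. Is going down the list likely?** With at most one child aged 1–4 per household, 40 such children need at least 40 participating households. Assume that 90% of households have a child of that age.
- If all take part, 40 / 0.90 ≈ 44 households are needed.
- If 90% take part, 40 / (0.90 × 0.90) ≈ 49 are needed, and the first 40 give 40 × 0.81 ≈ 32 children.

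So part of the extension is due to eligibility and part to non-participation.

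**4. Size of the bias (measles).** Inputs:
- V, the vaccinated share: 0.90, anchored on first-dose coverage above 90% (Background); 0.80 and 0.95 are assumed alternatives.
- s1, seropositivity in vaccinated children: 0.95, borrowing the first-dose effectiveness in Background.
- s0, seropositivity in unvaccinated children: 0, 0.20 or 0.40 (assumed).
- r1 and r0, participation of vaccinated and unvaccinated children: r1 = 0.90, r0 = 0.80, 0.70 or 0.50 (assumed).

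Formulas: true = V × s1 + (1 − V) × s0. Vaccinated share among participants, Vr = V × r1 / [V × r1 + (1 − V) × r0]. Observed = Vr × s1 + (1 − Vr) × s0.

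Worked case, V = 0.90, s0 = 0.20, r0 = 0.80: true = 0.855 + 0.020 = 0.875; Vr = 0.81 / 0.89 = 0.910; observed = 0.8826; bias +0.76 points.

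| V | s0 | True | r0 = 0.80 | r0 = 0.70 | r0 = 0.50 |
|---|---|---|---|---|---|
| 0.90 | 0 | 85.5% | +0.96 | +1.94 | +3.98 |
| 0.90 | 0.20 | 87.5% | +0.76 | +1.53 | +3.14 |
| 0.90 | 0.40 | 89.5% | +0.56 | +1.12 | +2.30 |
| 0.80 | 0.20 | 80.0% | +1.36 | +2.79 | +5.85 |
| 0.95 | 0.20 | 91.25% | +0.40 | +0.80 | +1.62 |

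Over V = 0.80–0.95, s0 = 0–0.40 and r0 = 0.50–0.80, the bias runs from +0.3 to +7.4 points. It is zero when r0 = r1, and upward whenever r0 < r1 and s0 < s1.

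**5. Against sampling error.** Ages 1–4: n = 25 × 40 = 1,000. With the plan's intraclass correlation of 0.01, the design effect is 1 + 39 × 0.01 = 1.39. Half-width at 87.5% = 1.96 × √(0.875 × 0.125 × 1.39 / 1,000) = 2.4 points. This leaves out any loss from unequal weights.

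**6. On the susceptible fraction.** In the 87.5% row, 12.5% are susceptible. Biases of 0.76 and 1.53 points understate that by 0.76 / 12.5 = 6% and 1.53 / 12.5 = 12%.

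**7. After correction.** Weighting participants by 1/r1 and 1/r0 within dose strata returns the true value in every case (for example 0.890 back to 0.875). This requires that participation depends on serostatus only through recorded dose, and that the dose records are complete.

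**The case against.** The best defence is that an article condenses its protocol, and that non-response weighting is the kind of detail left to an analysis plan. That would hold had the article been silent on weights. It prints the formula and names the adjustment, and neither has room for response by vaccination status.

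Several stronger readings are tempting, and the article does not support them:

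- *Refusers in the main sample are expressly replaced.* The article says this only for venous blood, and those children still give a dried blood spot. The Stage 3 top-up is triggered by a shortage of eligible children. Replacement of non-participants is inferred from the stopping rule in Stage 4.
- *Replacement causes the bias.* It does not. A fixed draw with the same selective non-response and no replacement would be just as biased. Selection by the statistician and data manager from a pre-randomised list is sound.
- *Refusals are hidden.* The consent log records them. Only children never contacted might go unlogged.
- *The weights ignore non-response altogether.* The age-by-cluster adjustment deals with differences between age groups and between clusters. What remains is the difference within a cell.
- *The bias conceals the immunity gaps.* Suppose participation depended on immunity itself, with 85% truly immune and 90% of them taking part. Participation of 80%, 70% or 60% among the non-immune gives 0.765/0.885 = 86.4%, 0.765/0.870 = 87.9% or 0.765/0.855 = 89.5%, all below the 92–95% band. That model also ties participation to antibody status, for which the article gives no basis. The bias crosses 92% only when the truth is just below it, as when 91.25% becomes 92.05% (V = 0.95, s0 = 0.20, r0 = 0.70).

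It also stands that no passage links non-participation to missed doses. Community and home sensitisation and finger-prick collection at home should help participation.

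**Conclusion.** The point holds as a conditional one. The weights as written cannot correct participation that differs by vaccination status within an age-by-cluster cell. If under-vaccinated children take part less, the bias is upward.

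Its size rests on assumed participation rates and assumed seropositivity in unvaccinated children. At 90% coverage and gaps of 10 to 20 points, it is about 0.6 to 1.9 points, less than the half-width of about 2.4 points for ages 1–4. At 80% coverage with s0 = 0.20, the same gaps give 1.4 to 2.8 points. Unlike sampling error, it does not shrink with more children. The article does not show that such bias will occur. It is worth guarding against because the means are largely in hand.

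**What to change.** 1. Record the final outcome of every child drawn: consented, refused, not contacted, or no eligible consenter. This extends the existing consent log to non-contacts.
2. Multiply the selection weight by a non-response factor estimated among all drawn children from site or district, age group and HDSS-recorded doses of measles-containing vaccine. Count measles-only and combined vaccine alike, because the combined vaccine came in only in 2017. Keep an unknown category and collapse sparse cells; two routine doses will not occur under 1 year, for example. Let c in the base weight count children drawn, so that average non-response is not counted twice, and apply the planned age-by-cluster adjustment last.
3. Report participation by HDSS dose status.
4. Use HDSS register totals for raking only as a sensitivity analysis. The HDSS covers consenting households, its records may be incomplete, and the article does not say whether they include campaign doses.

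The cost is field logging of non-contacts, some analysis work and slightly more variable weights. No extra children or blood samples are needed. Non-response that recorded doses do not explain stays uncorrected, and the report should say so.

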### Community and individual sensitization

To ensure ethical and comprehensive engagement, we will conduct both community and individual sensitization activities before obtaining informed consent and initiating any study procedures or data collection.

#### Community sensitization

Community sensitization will involve consultation with the Ministry of Health (both national and regional health directorates) and key stakeholders, including EPI program managers, representatives from WHO in The Gambia and district leadership. Before commencing study activities, we will organize a series of *kolanut* meetings with prominent leaders in the selected local communities [34]. These leaders include the District Chiefs, *Alkalos* (village/community leaders), other community elders, religious leaders, women’s and mothers’ group representatives, and other local advocates. The meetings will be held at accessible venues within the chosen survey communities.

During these meetings, we will discuss the details of the serosurvey, allowing ample time for questions to ensure that everyone present fully understands the purpose of the survey, as well as other key information, such as potential risks and benefits. The information provided will be based on the informed consent document (ICD) to ensure accuracy and consistency.

Following the meetings, we will disseminate information about the serosurvey through established community networks to reach a broader audience [34]. These engagements aim to foster understanding among influential community members, minimize misconceptions, and encourage accurate communication within the community. Feedback received during these sessions will guide the planning of individual sensitization activities.

#### Individual sensitization

After the community sensitization, we will conduct individual sensitization to provide more detailed information about the serosurvey directly to the parents or caregivers of children within the eligible age cohorts. During these visits, which will take place at the homes of the parents or caregivers of the selected children, the study team members will summarize the key information from the approved ICD.

Parents or caregivers will receive a copy of the ICD and be encouraged to review it with their partner and other significant family members. During this visit, we will also collect basic contact information, such as telephone numbers, to facilitate follow-up communication. A subsequent visit, scheduled at least 24 hours later, will provide an opportunity to address any additional questions and obtain formal informed consent. Only after obtaining this consent will any study procedures or data collection activities be initiated.

### Informed consent procedure

Before any study procedures or data collection take place, signed or thumb-printed, dated, and timed written informed consent and assent for participation in the serosurvey must be obtained using an ICD approved by the Gambia Government/MRC Joint Ethics Committee and the LSHTM Research Ethics Committee. The identity and age of all prospective participants will be confirmed using a suitable source document, such as a birth certificate, or the hand-held infant welfare card.

Written informed consent will be sought from all parents of the selected children within the eligible age cohorts. For children aged 6–11 years, we will also confirm their willingness to participate and document their verbal assent, while for those aged 12–14 years, we will seek written assent in addition to parental written informed consent. Study staff (nurses and field workers) with appropriate English and local language skills will obtain informed consent and assent. Consent can only be obtained from parents who are at least 18 years old. Therefore, if both parents of a child are under 18, the child cannot be enrolled in the study. Whether the process is conducted in English or a local language, the ICD will be reviewed line-by-line with the parent or caregiver by the staff conducting the consent process to ensure all details are understood. Self-reading alone will not suffice. During this review, opportunities for questions and clarifications will be provided. Since the local languages in The Gambia are primarily spoken and not widely written, the ICD will be provided in English and translated orally into the relevant local languages by the person obtaining consent.

Consent from a guardian, rather than a parent, will only be accepted if both parents are deceased or if both parents are out of The Gambia for an extended period, leaving another adult to care for the child. Guardians cannot provide consent if the parent is in another part of The Gambia or temporarily out of the country. A certified copy of the completed ICD will be provided to the parent or caregiver after the consent is signed or thumb-printed. The outcome of the informed consent process (i.e. consented/did not consent) will be recorded in the study’s consent log. As part of the informed consent process, consent will also be sought for storage of samples, the future use of any remaining samples and associated data for ethically approved research intended to benefit the people of The Gambia.

### Specimen and data collection

Specimen and data collection will be led by study nurses, who will be responsible for ensuring accuracy and completeness of information [34]. Sociodemographic data, vaccination history (campaign-based and routine vaccination), and any history of measles in the index child in the preceding one year will be collected from caregiver or parents and recorded using electronic Case Report Forms (eCRF). Hand held vaccination cards will serve as the primary sources of vaccination data, however, caregiver or parental recall will also be used when cards are unavailable. In addition, routinely collected vaccination records from the HDSS database will be used to supplement the data when needed.

Dried blood spots (DBS) will be collected from all children enrolled in the study and will occur in the participants’ home. To obtain the DBS, the fingertip of each child will be wiped clean with alcohol swabs and pricked using a contact-activated retractable lancet. Two to three blood droplets (approximately 150 μl of whole blood) [35] will be collected directly onto labeled *HemaSpot HF* device (SpotOnSciences, San Francisco, CA, USA) within 30 minutes of opening the device. The *HemaSpot HF* cartridge contains an absorbent collection matrix with a desiccant to protect the sample from moisture and the collection component is covered by an application surface with a small opening to allow biological fluids to enter. Once two to three drops of blood are collected, the cartridge will be closed within one minute, to allow the built-in desiccant to dry the sample within minutes. For DBS stability in our setting with high humidity, cartridges will be transported at ambient temperature from the field but stored at 4°C for longer periods in the lab [36]. All samples will be collected following universal precautions.

To compare the diagnostic accuracy of DBS with venous blood samples for estimating measles and rubella population immunity levels, an additional venous blood sample will be collected concurrently with the DBS from a randomly selected 10% of the study participants. Children will be eligible for venous blood collection if they are at least one-year-old, reside in a cluster with a health facility, and where samples can be transported to the laboratory within 30 minutes. Venous blood collection will take place in a health facility or similar setting within the selected clusters. For these participants, up to 2 ml of venous blood will be drawn into a serum separator tube, immediately following the collection of the DBS sample. Serum tubes will be gently inverted 5 times and the blood left to stand upright for 30 minutes at ambient temperature to allow clotting. Samples will then be stored at 4 to 8°C in cold boxes and transported to the laboratory. In the laboratory, specimens will be recentrifuged at 1000 g for 10 minutes and the sera aliquoted, labeled, and stored at − 20°C.

If a child or parent refuses venous blood collection, they will be replaced by another child from the same age cohort and cluster. However, only the DBS sample will be collected from the original child who declined the venous blood draw.

### Sample testing

Measles and rubella virus-specific immunoglobulin G (IgG) antibodies are well-established markers of immunity against infection and of vaccination. Paired DBS and serum samples will be tested on the same plate using commercially available anti-measles IgG and anti-rubella IgG enzyme immunoassay (EIA) kits (Euroimmun, Perkin Elmer, Germany) [36,37]. Serum samples will be processed according to the manufacturer’s protocol, with samples diluted 1:101 using the Euroimmun ELISA kit sample buffer prior to testing. DBS samples will first be eluted following a method described elsewhere [36]. Briefly, one wedge will be selected from each *HemaSpot HF* device and placed into a cryotube containing 100 μl of elution buffer. Tubes will be incubated for 2 hours at 37°C, with agitation for 20 minutes before and after incubation after which filter paper will be discarded and samples centrifuged followed by collection of eluate.

Based on extensive standardization testing for optimal elution and dilution ratios, 30 μl of eluted DBS will be diluted using 210 μl of the Euroimmun ELISA kit diluent, separately for both measles and rubella, at a 1:8 ratio for the DBS samples [36]. All subsequent steps for ELISA testing will be identical for sera and DBS. Seroprotection levels will be interpreted quantitatively and qualitatively based on the manufacturer’s recommendations. Near-real-time data management will be conducted to monitor variability. For quality assurance, a randomly selected stratified subset of serological samples, including all those with equivocal results, will be re-tested. If a specimen result remains equivocal after re-testing, it will be classified as negative to ensure consistency and to err on the side of slightly underestimating the population-level immunity prevalence. We plan to conduct all tests at the MRC Unit The Gambia serology laboratories. However, if this is not possible for any reason, we may ship the samples to another laboratory outside The Gambia for testing.

